Aim 1: Determine the clinician-reported feasibility of conducting a clinician-level, randomized controlled trial of TLT compared to usual care in the ED.

Hypothesis: TLT is feasible to conduct a clinical-level randomized study in the ED.

Aim 2: Determine the patient-reported acceptability of TLT in the ED.

Hypothesis: The patients or surrogates (if patients are unable to consent) randomized to TLT will feel more heard and understood about their end-of-life care wishes (primary outcome).

1. **GENERAL DESCRIPTION OF THE STUDY DESIGN**

Overview

To demonstrate the feasibility (Aim 1) and acceptability (Aim 2) of TLT, we will conduct a parallel group, clinician-level, pilot randomized clinical trial among 40 emergency clinicians (~20 in TLT and ~20 in usual care) in the ED.

Randomization: Using REDCap’s integrated randomization module,^24^ we will conduct clinician-level randomization using random blocks of four to ensure that emergency clinicians are evenly distributed one-to-one between intervention and control arms.

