| Patient-reported acceptability of TLT conversation (primary outcome)* | A 5-point Likert scale (i.e., “How acceptable was it for your doctor to talk to you about your expectations for ICU care?” and “How likely would you recommend this conversation for other patients like you?” “Not at all (1)” to “Completely (5)”). | Immediately after the TLT conversation |
| Heard and understood | A National Quality Forum endorsed, validated measure for palliative care modified to fit the context of serious illness conversations (“How well they feel heard and understood by your emergency department clinician about medical care they would want if they were to get sicker?” a 5-point Likert scale “Not at all (1)” to “Completely (5)”).^39^ | Immediately after the TLT conversation |
| Patient-reported end-of-life quality of communication | A validated, quality of end-of-life communication survey (4 items selected a priori, a 10-point Likert scale “Worst you can imagine (0)” to “Best you can imagine (10)”).^40^ | Immediately after the TLT conversation |
| Decisional regret scale | A validated survey that measures “distress or remorse after a [health care] decision” (5 items, 5-point Likert scale “Strongly agree (1)” to “Strongly disagree (5)”).^41^ | After 24 hours, 48 hours, and 1 week |
| Clinical outcomes abstracted from EHR | Number of days to the first family meeting in intensive care unit (ICU), ICU length of stay (LOS), hospital LOS, # family meetings, ICU procedures (e.g., CPR, pressors, etc.), ICU mortality, hospital disposition, hospice utilization. | After discharge or upon patient death |

A research assistant blinded to treatment allocation will perform all follow-up assessments. Our team will extract data from the EHR using a standardized approach.^42^

Study Termination:

We will follow the participating clinicians for up to one year to accrue an adequate number of patients they admit to the intensive care unit. Given that an emergency clinician may encounter ~3 to 10 seriously ill older adults being admitted to the intensive care unit per month, we estimate that it would take approximately one year to accrue ~10 patient/interventionist ED clinician who might meet the inclusion/exclusion criteria for Aim 2. The follow-up assessments of the patients will terminate when/if the participants die or are discharged from the hospital.

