Compared to the usual clinical care, we do not anticipate any additional risks or discomforts to our clinician or patient participants other than privacy/confidentiality risks. Several steps have been taken to maximize privacy. Questionnaires will be completed in private, walled ED treatment areas. Subjects will be assured that refusal to participate will not affect their care in any way. Unique identification numbers will be assigned to participants to link contact information and study data. These identification numbers do not contain patient identifying information. All research personnel involved in any way in this project will complete training in the protection of human research subjects per guidelines issued by the U.S. Department of Health and Human Services, Office for Human Research Protection. Staff training conducted by the candidate will include information about the importance of confidentiality and techniques to maintain confidentiality of all information reported by research participants. All study data will be collected and stored using REDCap. The purpose is to provide a system and associated support resources to enable efficient and high-quality collection and management of research data that is standards-based in design, development, and implementation. Standard features of electronic clinical research data management systems are available in the web-based systems provided with the service. These include interactive data entry with real-time field validation, lab data imports, audit logs to record database modifications, database integrity checks, security (in logins, permissions based on need, and encryption), reporting, forms inventory, and exports to common statistical packages for analysis. The database system provides for secure web-based data entry with the data stored on servers that maintained by Mass General Brigham. The data is encrypted during transmission. Consistent with NIH guidelines, a Data Safety Monitoring Committee (DSMC) will not be required for this single site, interventional trial.

1. **BENEFITS**

No proven benefits to the participants are expected. However, we hope that providing patient-centered structures to the usual care will improve the alignment of intensive care utilization with patients’ values and goals.

1. **STATISTICAL ANALYSIS**

**Aim 1: Determine the feasibility of conducting a clinician-level, randomized controlled trial of TLT compared to usual care.**

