**Aim 2: Determine the patient-reported acceptability of TLT in the ED.**

Hypothesis: The patients and surrogates undergoing TLT conversations will feel heard and understood about their end-of-life care wishes (primary acceptability outcome).

Descriptive statistics will be used for baseline characteristics of the study sample. We will compare patient demographics between study arms to assess randomization using two sample t-test or Wilcoxon rank sum test for continuous variables and chi-square for categorical variables. Within arms, we will use a one-sample binomial exact test of proportions for categorical outcomes (e.g., EHR documentation), and Wilcoxon signed ranks test for ordinal outcomes (e.g., Heard and Understood survey). A significance level, alpha, is set to 0.05. We will conduct a secondary analysis using linear mixed models at baseline and one month to include all non-missing data. The EHR-based outcome will be assessed using an EHR review. We will publish our findings regardless of the results and will follow the CONSORT guidelines for reporting RCT.^43^

**Sample Size:** No previous two-arm trial of TLT has been conducted; thus, the effect size remains unknown. Given the primary purpose of conducting a RCT is to demonstrate the feasibility of conducting a randomized design study, no gold standard for sample size calculations exists. However, prior literature suggest that 15 to 20 participants per group are required to ensure scientific validity of the pilot study results.^44^ Therefore, the present study will include a total of 32 participants with 16 participants per group. In addition, the results of this pilot study will provide information on the difference between groups and standard deviation necessary for sample size calculation during the future full-scale study.

1. **MONITORING AND QUALITY ASSURANCE**

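### The design section randomises 40 clinicians, the sample size paragraph says 32 participants of unnamed type, and no patient enrolment target is stated

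*Protocol*

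**What the plan says.** The Overview under General Description of the Study Design describes a "pilot randomized clinical trial among 40 emergency clinicians (~20 in TLT and ~20 in usual care) in the ED". The Randomization paragraph that follows makes the clinician the unit allocated: "we will conduct clinician-level randomization using random blocks of four".

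The Sample Size paragraph, at the end of Statistical Analysis, notes that the effect size is unknown and rests on a pilot rule of thumb: "prior literature suggest that 15 to 20 participants per group are required to ensure scientific validity of the pilot study results". It concludes that "the present study will include a total of 32 participants with 16 participants per group". The unit is not named.

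Three other places bear on the reading:

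- Risks and Discomforts speaks of "our clinician or patient participants", so the word participants covers both kinds of subject.
- Study Termination (in Study Procedures) says "an emergency clinician may encounter ~3 to 10 seriously ill older adults being admitted to the intensive care unit per month", and then "we estimate that it would take approximately one year to accrue ~10 patient/interventionist ED clinician who might meet the inclusion/exclusion criteria for Aim 2". It follows clinicians for no more than a year, to gather a number of patients described only as adequate.
- The recruitment text in Subject Selection caps non-Hispanic White enrolment at 70% of a target that is given no number.

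**The concern.** A trial's size should be stated once for each unit. Here the only two totals differ, nothing links them, and the one in the statistics section has no unit. The placement of the paragraph does not settle the matter. It follows the Aim 2 text, whose subjects are patients and surrogates, but its rationale is the feasibility of a randomised design, and the units randomised are clinicians.

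Two things depend on the answer. One is how many clinicians to recruit and randomise. The other is how many patients or surrogates to enrol, which fixes the ethnicity cap and the point within the year at which accrual is complete. The same paragraph expects the pilot to supply the between-group difference and SD for a full-scale trial, and the precision of both depends on the size and on the unit.

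**Working it through.** **Inputs.** 40 clinicians, about 20 per arm (Overview); 32 participants, 16 per group, and the 15 to 20 rule (Sample Size); about 10 patients per interventionist clinician, and 3 to 10 encounters per month (Study Termination); blocks of four (Randomization); the 70% cap (Subject Selection); the criterion of more than 70% of intervention clinicians (Statistical Analysis, Aim 1). The protocol gives no effect size, SD, attrition rate, intraclass correlation (ICC) or precision target, so there is no formula to reproduce.

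**The paragraph on its own.** 2 × 16 = 32, and 16 lies within 15 to 20, so it agrees with itself. But 20 per arm also lies within 15 to 20, so the rule cannot choose between the figures. Nor can the block size: 40/4 = 10 and 32/4 = 8 are both whole numbers.

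**Reading 1: the 32 are clinicians.** 16 against about 20 per arm; (40 − 32)/40 = 20% fewer. The approximation sign in the Overview is on the arm sizes, not on the total of 40.

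**Reading 2: the 32 are patients.** 32/40 = 0.8 patients per clinician, and 16/20 = 0.8 within each arm. The accrual estimate is about 10 per interventionist clinician.

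**Reading 3: the 32 are those evaluable out of 40.** Enrolled = evaluable/(1 − attrition):

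- 10%: 32/0.90 = 35.6, so 36
- 15%: 32/0.85 = 37.6, so 38
- 20%: 32/0.80 = 40
- 25%: 32/0.75 = 42.7, so 43

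Only the 20% line gives 40, and the protocol states no such allowance.

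**Precision if the unit is the clinician.** The 95% half-width for a between-arm difference, with one independent value per clinician, is t × √(2/n) in SD units:

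- n = 16: 2.042 × √(2/16) = 0.72 SD
- n = 20: 2.024 × √(2/20) = 0.64 SD

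For the one-arm clinician criterion, the smallest counts above 70% are 12/16 and 15/20. Their exact 95% intervals are 48% to 93% and 51% to 91%.

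**Precision with clustered patients (assumption-dependent).** Assume 10 enrolled patients per clinician in both arms and an ICC of 0.05 to 0.10; the protocol states neither. The design effect is 1 + 9 × ICC = 1.45 to 1.90. The half-width 1.96 × √(2 × design effect/n) is then:

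- 16 clinicians, n = 160 per arm: 0.26 to 0.30 SD
- 20 clinicians, n = 200 per arm: 0.24 to 0.27 SD

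**The cap.** If the target were 32 patients, 70% would be 22.4, so 22. If it were the 20 × 10 = 200 possibly eligible patients of the intervention arm, 70% would be 140. The protocol does not say which, if either, applies.

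**The case against.** A reader might infer three rival sample sizes and conclude that the patient total is uncertain by a factor of 6 to 12 (32 against 200 to 400), with precision differing about threefold (0.72 against 0.24 SD). The protocol does not support that. The figure of about 10 per interventionist clinician is an approximate accrual estimate for patients who may turn out to be eligible. It is a number per clinician, compatible with either 40 or 32 clinicians, and it conflicts with 32 only if the 32 are patients. The totals of 200 and 400 treat possibly eligible patients as enrolled, and 400 also gives control clinicians a yield that no section states. The half-widths for 200 per arm rest on the same control assumption and on an assumed ICC.

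A reader might also infer that accrual has no end. It does: the one-year limit applies under either figure. What is undefined is the number at which accrual would be complete before then.

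Other points in the plan's favour also stand. A pilot needs no power calculation. If participants means clinicians, both figures meet the cited rule and the loss of precision is small. The outcomes labelled primary in Table 2 come from the intervention arm only, so between-arm precision is not the measure for them. Adding confidence interval widths to the sample size paragraph would be a reporting preference, and a separate analysis plan may hold them.

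None of this reconciles 40 with 32, names the unit, or supplies the patient target to which the cap refers.

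**Conclusion.** The point holds as an internal inconsistency, not as a failed calculation. The Overview and the Sample Size paragraph give different totals in the same protocol version, and each natural reading of the 32 either conflicts with another statement or needs an attrition allowance that is not stated. On the clinician reading the gap is 8 clinicians (20%) and the cost in precision is modest: 0.72 against 0.64 SD. That comparison assumes one independent value per clinician. On the patient reading, 0.8 per clinician is far below the accrual estimate, but the resulting loss of precision cannot be stated without assuming an ICC, equal control accrual and full enrolment of possibly eligible patients.

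Separately, there is no patient enrolment target, so the 70% cap cannot be applied as written. The contradiction should be corrected because recruitment relies on the figure, although its effect on precision may be small.

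**What to change.** - Make the Overview and the Sample Size paragraph agree on one number of clinicians randomised per arm. Alternatively, state that 32 is the minimum evaluable out of 40 randomised, and give the 20% attrition that this implies.
- Name the unit of the 32.
- State the target number of patients or surrogates per clinician and per arm, including control, and say whether the figure of about 10 is a target or a pool of possibly eligible patients.
- Refer the 70% cap and the end of accrual to that target, and keep the one-year limit.
- If precision is quoted for clustered patients, mark it as depending on an assumed ICC and on assumed equal accrual in the control arm.

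The cost is a rewritten Sample Size paragraph and short matching edits in the Overview, the recruitment text and Study Termination. The correction itself calls for no extra enrolment.

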**Describe the plans that will be followed by study staff for monitoring and quality assurance, including:**

- **Adverse event (AE) criteria and reporting procedures**

Any AE will be reported to our institutional review board at the time of annual continuing review by the principal investigator using an AE Form in accordance with the Partners Human Research Committee guidelines for AE reporting.

- **Planned safety monitoring**

The proposed research is a minimal risk study and does not meet the criteria for an NIH-defined Phase III trial given no patient outcomes will be collected. Therefore, a data and safety monitoring board will not be required, and the PI will be solely responsible for data and safety monitoring of the proposed research. In the event of an adverse event, the research team will report immediately to the PI, who will be responsible for management and reporting to the IRB, and to the NIH institute.

- **Outcomes monitoring, including planned frequency of review**

Not applicable.

- **Study stopping rules as applicable**

Unanticipated Problems (UP): As with any AE above, the PI will report any UP within 5 working days / 7 calendar days of the date. The investigator first becomes aware of the problem using an Adverse Event Form in accordance with the Partners Human Research Committee guidelines for AE reporting, please see attached institutional policy.

- **Internal monitoring of source data, protocol adherence, and recordkeeping, including which staff will be responsible and planned frequency of review**

The PI is responsible for monitoring and recordkeeping on REDCap.

- **Independent monitoring of source data as applicable**

All personal health information will be removed from the research data from the participants and clinicians at the earliest possible time. All data will be stored in a secured Mass General Brigham approved shared drive accessible only to the study staff. Recordings will be stored on an encrypted recording device and saved to the secure Mass General Brigham-approved shared drive.

1. **PRIVACY AND CONFIDENTIALITY**

Study procedures will be conducted in a private setting

Only data and/or specimens necessary for the conduct of the study will be collected

Data collected (paper and/or electronic) will be maintained in a secure location with appropriate protections such as password protection, encryption, physical security measures (locked files/areas)

Specimens collected will be maintained in a secure location with appropriate protections (e.g. locked storage spaces, laboratory areas)

Data and specimens will only be shared with individuals who are members of the IRB-approved research team or approved for sharing as described in this IRB protocol

Data and/or specimens requiring transportation from one location or electronic space to another will be transported only in a secure manner (e.g. encrypted files, password protection, using chain-of-custody procedures, etc.)

All electronic communication with participants will comply with Mass General Brigham secure communication policies

Identifiers will be coded or removed as soon as feasible and access to files linking identifiers with coded data or specimens will be limited to the minimal necessary members of the research team required to conduct the research

All staff are trained on and will follow the Mass General Brigham policies and procedures for maintaining appropriate confidentiality of research data and specimens

The PI will ensure that all staff implement and follow any Research Information Service Office (RISO) requirements for this research

Additional privacy and/or confidentiality protections

1. **REFERENCES**

